#### **4.6.3.1. Compliance and adherence**

If a participant in a control group receives antiseptic skin application, this may be due either to inadvertent application (e.g. due to error thinking the participant is in an intervention group), or due to routine use of antiseptic. Both will be recorded on trial CRFs. In the case of use for a specific purpose related to routine clinical care, this will be recorded but not classified as a protocol deviation, whereas if a participant inadvertently receives an application designed for a participant randomised into an intervention group, then this will be recorded as a protocol deviation.

#### **4.6.4. Unblinding/unmasking**

NeoVT-AMR is an open label trial and therefore there is no unblinding/unmasking.

#### **4.6.5. Protocol treatment discontinuation**

In consenting to the trial, mothers and parents/carers are consenting to trial treatment, trial follow-up and data collection. However, a participant may stop treatment early for any reason, including:

Both strata:

- Withdrawal of consent for treatment by the mother or parent/ carer
- Unacceptable toxicity or adverse event
- Intercurrent illness that prevents further treatment
- Any change in the participant's condition that justifies the discontinuation of treatment in the clinician's opinion
- Inadequate compliance with the protocol treatment in the judgement of the treating clinician

As participation in the trial is entirely voluntary, the mother or parent/carer may choose to discontinue the trial treatment at any time without penalty or loss of benefits to which they are otherwise entitled. Although the mother or parent/carer is not required to give a reason for discontinuing their trial treatment, a reasonable effort should be made to establish this reason while fully respecting their rights.

Participants should remain in the trial for the purpose of follow-up and data analysis (unless the mother or parent/carer withdraws their consent from all stages of the trial). If a participant is withdrawn from follow-up, refer to [Section 4.7.4](#).

#### **4.6.6. Compliance and adherence**

Adherence to allocated interventions will be recorded on CRFs/worksheets.

#### **4.6.7. Non-trial treatment**

##### **4.6.7.1. Medications permitted**

After entry into the trial, any concomitant medication which is required is permitted, including any antimicrobials. All antiseptics and antibiotics will be recorded on CRFs.

##### **4.6.7.2. Medications not permitted**

All medications are permitted if necessary as deemed by participant's medical team.

##### **4.6.7.3. Medications to be used with caution**

Iodine has a known cosmetic interaction with octenidine. If applied within four hours of one another, the skin will discolour to a deep purple colour, which has no clinical significance and fades completely over

time. The exclusion criteria for both the labouring women and neonates exclude patients with any planned iodine use. In the case where iodine is needed and octenidine has been applied as part of the trial, chlorhexidine will be used instead of iodine. This is in line with latest WHO guidance.

Chlorhexidine may be required for routine care in any group, such as an invasive procedure or cord care. Whenever used outside of the trial procedures this will be recorded in the CRF and will not be considered as a protocol deviation if it is for routine care.

#### 4.7. Assessments and follow-up

##### 4.7.1. Trial assessment schedule

##### 4.7.1.1. Maternal strata

**Table 1: Trial procedures in maternal strata**

| Visit number                                                         | 1         |               | 2   | 3   | 4   | 5    | 6    | 7    | 8             | 9               |
|----------------------------------------------------------------------|-----------|---------------|-----|-----|-----|------|------|------|---------------|-----------------|
| Visit name                                                           | Screening | Randomisation |     |     |     |      |      |      | Post delivery | Final follow up |
| Day in trial                                                         | 0         | 0             | 0   | 0   | 0   | 1    | 1    | 1    |               | 28              |
| Time in trial                                                        |           |               | 0hr | 4hr | 8hr | 24hr | 28hr | 32hr |               |                 |
| All participant mothers                                       |           |               |     |     |     |      |      |      |               |                 |
| Eligibility                                                          | X         |               |     |     |     |      |      |      |               |                 |
| Participant Information Leaflet                                      | X         |               |     |     |     |      |      |      |               |                 |
| Informed consent                                                     | X         |               |     |     |     |      |      |      |               |                 |
| Enrolment form and randomisation                                     |           | X             |     |     |     |      |      |      |               |                 |
| Baseline data collection                                             |           | X             |     |     |     |      |      |      |               |                 |
| Newborn's swabs (peri-rectal/rectal + cervical/neck) - post delivery |           |               |     |     |     |      |      |      | X             |                 |
| Final follow up                                                      |           |               |     |     |     |      |      |      |               | X               |
| Participants in single application arms                       |           |               |     |     |     |      |      |      |               |                 |
| Antiseptic application                                               |           |               | X   |     |     |      |      |      |               |                 |
| Clinical assessment (toxicity + AE)                                  |           |               | X   | X   | X   | X    | X    | X    | X             |                 |
| Swabs (vaginal + perineal)                                           |           |               | X   | X   | X   | X    | X    | X    |               |                 |
| Participants in multiple application arms (4hrly)             |           |               |     |     |     |      |      |      |               |                 |
| Antiseptic application                                               |           |               | X   | X   | X   | X    | X    | X    |               |                 |
| Clinical assessments (toxicity + AE)                                 |           |               | X   | X   | X   | X    | X    | X    | X             |                 |
| Swabs (vaginal + perineal)                                           |           |               | X   | X   | X   | X    | X    | X    |               |                 |
| Participants in control group                                 |           |               |     |     |     |      |      |      |               |                 |
| Clinical assessments (toxicity + AE)                                 |           |               | X   | X   | X   | X    | X    | X    | X             |                 |
| Swabs (vaginal + perineal)                                           |           |               | X   | X   | X   | X    | X    | X    |               |                 |

On days assigned to maternal recruitment, eligibility will be assessed by trial midwives. Labouring women who meet all of the inclusion and none of the exclusion criteria will be provided with a participant information leaflet, have the trial verbally explained and given the opportunity to have their questions answered. Informed consent will be recorded ([Section 4.5.3](#)).

An enrolment form will be completed and data entered into the database. Participants will be randomised ([Section 4.5.5.1](#)) and have baseline data collected, including medical history, gestational age, co-morbidities and antibiotic history.

Assessment and treatment regime will be according to allocation:

### **All maternal participants:**

Toxicity assessment: the toxicity assessment will include both questions about symptoms (of irritation) and a visual inspection of the vulval area (for erythema, skin breakdown and swelling) by trial staff. The assessment will take place immediately before the swabs at 4 hourly intervals during working hours on day 1 and day 2, or until birth if sooner and post delivery. More details can be found in [Section 4.7.3](#) and [Appendix II](#).

Swab: Swabs (low vaginal and perineal) will be taken at baseline (0 hr) and then 4 hourly on day 1 and day 2 (during working hours), or until birth (whichever is first). The swab timing will be recorded in a CRF. See MOP for further details on how to take swabs.

If the vaginal and perineal area is heavily soiled prior to the swabs and antiseptic application, it will be cleaned, as per routine clinical practice. Further details can be found in the MOP.

Swab of babies: Babies born to enrolled mothers will have swabs (peri-rectal/rectal and cervical/neck) collected after birth to assess bacterial load. The time this is taken will be recorded.

Final follow-up: On day 28 (+/- 7 days) after enrolment, final follow up will occur either by phone call or hospital visit. If a hospital visit is chosen, appropriate compensation will be provided for travel and time in line with local standard policies. Vital status will be ascertained, together with occurrence of adverse events (including clinically defined sepsis and any unscheduled visits to healthcare providers) and follow up of any reported potential side effects that were present.

### **Maternal participants in single application arms:**

Antiseptic: The antiseptic will be applied once to the vagina and perineum (more details [Section 4.6.2.1](#)) after the 1st assessment and swab. Following this, routine care at vaginal examination's will continue. Any antiseptic that is applied as part of routine care will be recorded on the CRF.

### **Maternal participants in multiple application arms:**

Antiseptic: The antiseptic will be applied to the vagina and perineum 4 hourly during working hours, up to a maximum of 6 times (more details [Section 4.6.2.1](#)), after each swab and assessment of toxicity.

### **Maternal participants in control group:**

Antiseptic application: any antiseptic that is applied as part of routine care will be recorded on the CRF. Antiseptic will be applied after the toxicity assessment and swabs.

Recruitment will continue until the sample size has been met. Missing swabs and incomplete follow up will be monitored closely and additional patients may be recruited to meet the required number of swabs.

**4.7.1.2. Neonatal strata****Table 2: Trial procedures in neonatal strata**

| Visit number                                                 | 1         |               | 2            | 3 | 4 | 5 | 6         |
|--------------------------------------------------------------|-----------|---------------|--------------|---|---|---|-----------|
| Visit name                                                   | Screening | Randomisation | Intervention |   |   |   | Follow up |
| Day in trial                                                 | 0         |               | 0            | 1 | 2 | 3 | 28        |
| All participant neonates                                     |           |               |              |   |   |   |           |
| Eligibility                                                  | X         |               |              |   |   |   |           |
| Parent/carer information leaflet                             | X         |               |              |   |   |   |           |
| Informed consent                                             | X         |               |              |   |   |   |           |
| Enrolment form and randomisation                             |           | X             |              |   |   |   |           |
| Baseline data collection                                     | X         |               |              |   |   |   |           |
| Assessment and treatment according to allocation (see below) |           |               |              |   |   |   |           |
| Final follow up                                              |           |               |              |   |   |   | X         |
| Participants in single application arms                      |           |               |              |   |   |   |           |
| Clinical assessment (temperature, skin score + AE)           |           |               | X            | X | X | X |           |
| Swabs (peri-rectal/rectal and cervical/neck)                 |           |               | X            | X | X | X |           |
| Antiseptic application                                       |           |               | X            |   |   |   |           |
| Participants in multiple application arm (24 hourly)         |           |               |              |   |   |   |           |
| Clinical assessment (temperature, skin score + AE)           |           |               | X            | X | X | X |           |
| Swabs (peri-rectal/rectal and cervical/neck)                 |           |               | X            | X | X | X |           |
| Antiseptic application                                       |           |               | X            | X | X | X |           |
| Participants in control group                                |           |               |              |   |   |   |           |
| Clinical assessment (temperature, skin score + AE)           |           |               | X            | X | X | X |           |
| Swabs (peri-rectal/rectal and cervical/neck)                 |           |               | X            | X | X | X |           |

Eligibility will be checked by trial staff. Parents/carers of neonates who meet all of the inclusion and none of the exclusion criteria will be provided with a participant information sheet, have the trial verbally explained and given the opportunity to have their questions answered. Informed consent will be recorded (Section 4.5.3).

An enrolment form will be completed and data entered into the database. Participants will be randomised (details in [Section 4.5.5.1](#)) and have baseline data collected, including antenatal history, estimated gestational age, birth weight, labour duration, mode of delivery, co-morbidities, and intrapartum and postpartum antibiotic history.

Assessment and treatment regime will be according to allocation:

### **All neonatal participants:**

Skin score: Skin will be assessed according to the skin score in Appendix I before each swab or antiseptic application at screening and once daily thereafter (at 24 and 48 hours) until discharge or 72 hours. For babies assigned to antiseptic application, skin score will also be assessed 30 minutes after antiseptic application.

Swab: Swabs (peri-rectal/rectal and cervical/neck) will be taken at baseline (0 hrs) and then at 24 hours, 48 hours, and 72 hours, or until discharge (whichever is sooner).

The timing of swabs will be recorded in a CRF. See MOP for further details on how to take swabs.

Final follow-up: On day 28 (+/- 7 days) after enrolment final follow up will occur either by phone call or hospital visit. If a hospital visit is chosen by the parents/carers, appropriate compensation will be provided for travel and time in line with local standard policies. Vital status will be ascertained, together with occurrence of serious adverse events (including clinically defined sepsis and any unscheduled visits to healthcare providers).

### **Neonatal participants in single application arms:**

Temperature: Temperature will be measured before antiseptic application, 15 minutes post application and once daily before the swabs thereafter until discharge or 72 hours.

Antiseptic: The antiseptic will be applied to the whole body (except face) (more details [Section 4.6.2.3](#)) after the 1st swabs.

### **Neonatal participants in multiple application arms:**

Temperature: Temperature will be measured before every antiseptic application and 15 minutes post application.

Antiseptic: The antiseptic will be applied to the whole body (except face) after each assessment and swabs: at baseline, and at 24 hours, 48 hours and 72 hours or discharge (more details [Section 4.6.2.3](#)).

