#### **4.6.2.1.2. Neonatal strata**

CHG is used in neonatal units (NNUs) in concentrations from 0.2-4%(40–43). Previous large- scale studies of CHG to decolonise neonatal skin have used concentrations towards the lower end of the range(22); however babies born in LMIC with high levels of environmental contamination may require relatively high concentrations to achieve effective decolonisation. This study will use an upper limit of 2% CHG because of rare reports of skin damage with concentrations of CHG  $\geq 2\%$ , although these are mostly limited to infants <1000g at birth(44). This trial is only recruiting neonates with a birth weight >1000g. OCT 0.1% and 0.1% Octenidine 2% Phenoxyethanol (OHP) are the standard antiseptics in neonatal unit's in Germany and there are published data on safety in neonates(16), including premature newborns(45). This study of OHP in premature newborns also demonstrated that although phenoxyethanol undergoes cutaneous absorption, it almost completely metabolizes to 2-phenoxyacetic acid, which can be detected in the urine. As with the maternal strata, OHP will be tested at a single concentration because of limited published data.

Previous studies from high income countries have documented a significant decline in skin bacterial load for up to 48 hours following a single topical application of CHG(14), however infants from LMIC may be exposed to high levels of environmental contamination during birth and in the postnatal period. This study will therefore compare a single antiseptic application to 24 hourly repeat applications until discharge, up to a maximum of 72 hours. Twenty-four hourly applications were selected as the maximum feasible to scale up in a LMIC setting. A control arm receiving standard of care will also be recruited.

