#### **4.6.2.7. Handling cases of overdose**

For the purposes of this trial, overdose will be defined as more than 4 hourly in the mothers or more than once daily application in the neonates. Any additional doses given will be recorded on the treatment CRF and an AE form completed. Adverse reactions due to this would be expected to be similar to those described in [Section 4.7.3](#) and will be recorded and reported in the same way as other adverse reactions (see [Section 5](#)).

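### The neonatal multiple-application schedule names discharge as an application time where other sections stop treatment at discharge, and its 72-hour application follows the last swab and last daily skin score

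*Protocol*

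**What the plan says.** **Application times.** In section 4.7.1.2, the paragraph on the multiple-application arms puts antiseptic after the assessment and swabs on each occasion, "at baseline, and at 24 hours, 48 hours and 72 hours or discharge". Table 2 marks clinical assessment, swabs and application on days 0, 1, 2 and 3. It has no discharge visit.

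**Discharge as an end point.** Section 4.6.2.1.2 describes "24 hourly repeat applications until discharge, up to a maximum of 72 hours". Section 4.6.2.6 uses discharge or 72 hours as the end of neonatal treatment, and section 9.1 says that application and trial procedures end at discharge.

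**Swabs.** Section 4.7.1.2 has them at baseline and then at "24 hours, 48 hours, and 72 hours, or until discharge (whichever is sooner"). Section 4.7.2 instead lists the final neonatal swab as one taken at discharge or 72 hours.

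**Overdose.** Section 4.6.2.7 counts as overdose "more than once daily application in the neonates" and adds: "Any additional doses given will be recorded on the treatment CRF and an AE form completed". Section 5.1.4 lists overdose without signs or symptoms among the things that are not adverse events.

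**Safety checks.** Skin is scored daily, before the swab or application, until discharge or 72 hours. After each application there is a temperature at 15 minutes and a skin score at 30 minutes. At day 28 the neonatal contact records vital status "together with occurrence of serious adverse events (including clinically defined sepsis" and unscheduled healthcare visits). Section 5.2, by contrast, has the non-serious AEs of Appendix III documented at each scheduled visit.

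**The concern.** Three things do not fit together.

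First, it is unclear whether a baby leaving between two 24-hourly time points is due an application on leaving. If so, a site following the schedule could give a whole-body application within hours of the previous one and have to ask whether it has caused an overdose under the protocol's own definition.

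Second, the overdose section asks for an AE form in a situation that the exemption list does not treat as an AE. Sites may then record the same event differently, which affects the AE tabulations.

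Third, because every swab and daily score precedes the application at the same time point, the 72 h application has no later swab or daily score. The pilot is meant to select a regimen for a larger trial, so readers should know how much of the four-application regimen the bacterial-load data describe, and what is asked about the skin after the last application.

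**Working it through.** No sample-size or power figure depends on this point. The check sets the times against each other.

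**1. Applications and swabs for a baby staying 72 h** (4.7.1.2 and Table 2, swab before application):

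| Application | Next swab | Next daily skin score |
|---|---|---|
| 0 h | 24 h | 24 h |
| 24 h | 48 h | 48 h |
| 48 h | 72 h | 72 h |
| 72 h | none | none |

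The 72 h swab therefore reflects three applications. One of four scheduled applications (1/4 = 25%) has no later swab or daily score. The arms concerned hold 3 × 21 = 63 neonates. This does not depend on how discharge is read.

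**2. Gap before a discharge application, if one is due.** For discharge at T hours, gap = T − (last scheduled time before T).
- T = 26: 26 − 24 = 2 h.
- T = 32: 32 − 24 = 8 h.
- T = 54: 54 − 48 = 6 h.

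Of the whole-hour times from 1 to 71, only 24 and 48 fall on schedule, so the gap is under 24 h at 71 − 2 = 69 of 71. This counts possible times. It is not a frequency, because the protocol gives no discharge times.

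**3. If daily means calendar day.** Assume discharge at whole hours from 08:00 to 17:00. Each baseline clock time below then leaves 27 off-schedule discharge times before 72 h.
- Baseline at 10:00: gaps of 1 to 7 h stay on the same day as the previous application, giving 7 × 3 = 21 of 27.
- Baseline at 16:00: only a 1 h gap does, giving 1 × 3 = 3 of 27.

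The conflict shrinks on this reading but remains.

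**4. If discharge only ends the schedule** (4.6.2.1.2, 4.6.2.6, 9.1), no extra application is given. The overdose conflict in steps 2 and 3 then does not arise; step 1 is unchanged.

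**5. Skin scores over a 72 h stay.** Multiple arms: 4 daily + 4 at 30 minutes = 8. Single arms: 4 daily + 1 at 30 minutes = 5. In the multiple arms, next-day scores follow the first three applications.

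**6. Day-28 scope.** Table 2 numbers day 28 as visit 6, so section 5.2 would have non-serious Appendix III AEs documented there. Section 4.7.1.2 names only vital status, serious events and unscheduled visits, and Table 2 leaves the clinical-assessment rows blank at day 28. Section 5.1.2 handles neonatal skin reactions separately from the graded AEs. The text at hand does not include Appendix III, so whether its list would pick up a late skin reaction cannot be checked.

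**The case against.** The strongest reply is that the overdose conflict rests on one phrase. Three other sections treat discharge as a stopping point, the footnote to Table 3 does the same for swabs, and Table 2 has no discharge column. The AE-form duty also attaches to additional doses, and a dose that the schedule calls for is arguably not additional. This stands in part: the conflict is conditional. The phrase is not an isolated slip, though, since section 4.7.2 names discharge as a swab time in the same way. A site could reasonably act on either version.

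A second reply is that swabbing before each application is deliberate. It measures the residual effect 24 h later at the same times in every arm, and the randomised contrast is single against 24-hourly application, not a count of four. That is right, and no estimate or test is wrong because of it. It only limits what the swabs can show about the last application.

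A reader might also infer three stronger things that the documents do not support:
- **That non-serious skin effects after the last application are never asked about.** Section 5.2 covers non-serious AEs at each scheduled visit, section 4.7.6 gives parents signs to watch for and contact details, and the day-28 contact covers unscheduled healthcare visits.
- **That skin toxicity is under-counted in the multiple arms.** With eight scores against five over a full stay, this is not shown.
- **That the last application yields no data.** It feeds the before-and-after temperature analysis in 4.10.4 and the 30-minute skin score.

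Finally, an AE form could serve to document an overdose that is not then counted as an AE. That is a workable practice, but the protocol does not say that it is the intended one.

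**Conclusion.** The point holds, and it is minor. The protocol contradicts itself on whether an application is due at discharge. On the reading that it is, an off-schedule discharge puts the application less than 24 h after the previous one (8 h for discharge at 32 h), which can meet the protocol's overdose definition. This rests on taking discharge in 4.7.1.2 as an application time, and its frequency cannot be estimated. The mismatch between 4.6.2.7 and 5.1.4 on recording overdose stands on either reading.

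Also on either reading, the swabs reflect at most three applications, in up to 63 neonates. After a 72 h application the specified follow-up is a 15-minute temperature, a 30-minute skin score and a day-28 contact whose scope is stated in two different ways. These are matters of wording and interpretation; the randomised comparison of bacterial load is not invalidated.

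**What to change.** - Reconcile sections 4.6.2.1.2, 4.6.2.6, 4.6.2.7, 4.7.1.2 with Table 2, 4.7.2, 5.1.4 and 9.1 on whether an application is due at discharge or at 72 hours, so that no scheduled application also counts as overdose and overdose is recorded in one way. Which schedule is right is for the sponsor to decide.
- Reconcile the neonatal day-28 content in 4.7.1.2 with section 5.2. In all neonatal arms, have that existing contact ask about skin reactions since the last in-hospital assessment.
- State that the efficacy evidence for the neonatal multiple-application regimen reflects at most three applications.

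The cost is a wording amendment and one question at a call or visit that already takes place. The downsides are that parental recall is less precise than a direct skin score, and that the efficacy claim for the multiple regimen becomes slightly narrower.
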